#### Nasal polyposis

- ☐ Yes
- ☐ No or very unlikely[L][SEP]
- ☐ Unknown

[L][SEP]

#### Aspirin intolerance

- ☐ Yes
- ☐ No or very unlikely[L][SEP]
- ☐ Unknown

[L][SEP]

#### Vocal cord dysfunction

- ☐ Yes
- ☐ No or very unlikely[L][SEP]
- ☐ Only in the past
- ☐ Unknown

#### Hyperventilation syndrome and/or panic disorder

- ☐ Yes
- ☐ No or very unlikely[L][SEP]
- ☐ Only in the past
- ☐ Unknown

#### Depression

- ☐ Yes
- ☐ No or very unlikely[L][SEP]
- ☐ Only in the past
- ☐ Unknown

#### Gastroesophageal reflux

- ☐ Yes
- ☐ No or very unlikely[L][SEP]
- ☐ Only in the past
- ☐ Unknown

Frequent (>2/yr) respiratory infections requiring antibiotics?

- ☐ Yes
- ☐ No or very unlikely[SEP]
- ☐ Only in the past
- ☐ Unknown

Bronchiectasis

- ☐ Yes
- ☐ No or very unlikely[SEP]
- ☐ Unknown

EGPA (Churg-Strauß-Syndrome)

- ☐ Yes
- ☐ No or very unlikely[SEP]
- ☐ Unknown

Eosinophilic pneumonia

- ☐ Yes
- ☐ No or very unlikely[SEP]
- ☐ Only in the past
- ☐ Unknown

ABPA (Allergic bronchopulmonary aspergillosis)

- ☐ Yes
- ☐ No or very unlikely[SEP]
- ☐ Unknown

Chronic heart failure

- ☐ Yes
- ☐ No or very unlikely[SEP]
- ☐ Only in the past
- ☐ Unknown

OSA (Obstructive sleep Apnea)

- ☐ Yes
- ☐ No or very unlikely[SEP]
- ☐ Only in the past
- ☐ Unknown

Other co-morbidities

-----  
-----

Has adherence to therapy ever been checked?

- ☐ Yes  
☐ No[L]SEP

If yes, please report date of most recent result:

% ICS taken (per period checked): \_\_\_\_\_%

Has Inhalation technique been checked?

- ☐ Yes  
☐ No[L]SEP

If yes, date last instruction:

Does the patients currently take one or more of the following medications

If yes, which one and at what dose?

- ☐ SABA
- salbutamol  $\leq$  8 puffs/day
  - salbutamol  $>$  8 puffs/day
  - terbutaline  $\leq$  8 puffs/day
  - terbutaline  $>$  8 puffs/day
- ☐ Anticholinergics
- ipratropium
- ☐ Fixed SABA/anticholinergic combinations
- ipratropium / fenoterol  $\leq$  8 puffs/day
  - ipratropium / fenoterol  $>$  8 puffs/day
  - ipratropium / salbutamol  $\leq$  8 puffs/day
  - ipratropium / salbutamol  $>$  8 puffs/day
- ☐ LABA single inhaler
- formoterol[L]SEP \_\_\_\_\_ ug/day
  - salmeterol[L]SEP \_\_\_\_\_ ug/day
  - indacaterol \_\_\_\_\_ ug/day
  - olodaterol \_\_\_\_\_ ug/day

- ☐ ICS single inhaler
  - beclomethasone \_\_\_\_\_ug/day
  - budesonide[SEP]\_\_\_\_\_ug/day
  - fluticasone[SEP]\_\_\_\_\_ug/day
  - ciclesonide \_\_\_\_\_ug/day
- ☐ LAMA single inhaler:
  - tiotropium: \_\_\_\_\_ µg/day[SEP]
  - glycopyrronium:\_\_\_\_\_ µg/day
  - aclidinium: \_\_\_\_\_ µg/Day
- ☐ Fixed ICS/LABA combination inhaler
  - budesonide / formoterol
    - budesonide \_\_\_\_\_ µg/day and fFormoterol\_\_\_\_\_ µg/day
  - salmeterol / fluticasone
    - salmeterol \_\_\_\_\_ µg/day and Fluticasone propionate\_\_\_\_\_ µg/day
  - beclomethasone / formoterol
    - beclomethasone \_\_\_\_\_ µg/day and formoterol \_\_\_\_\_ µg/day
  - fluticasone / formoterol
    - fluticasone \_\_\_\_\_ µg/day and formoterol \_\_\_\_\_ µg/day
  - fluticasone furoate/ vilanterol[SEP]
    - fluticasone fuorate \_\_\_\_\_ µg/day and vilanterol \_\_\_\_\_ µg/day
- ☐ Fixed LABA/LAMA combination inhaler
  - indacaterol / glycopyrronium
    - indacaterol \_\_\_\_\_ µg/day and glycopyrronium\_\_\_\_\_ µg/day
- ☐ montelukast
- ☐ theophylline
- ☐ Maintenance oral corticosteroids
  - predniso(lo)ne[SEP]\_\_\_\_\_ mg/day
  - dexamethasone \_\_\_\_\_ mg/day
  - betamethasone \_\_\_\_\_ mg/Day
  - hydrocortisone \_\_\_\_\_ mg/Day
  - triamcinolone (injections) \_\_\_\_\_ mg/month

Is patient currently tapering his/her oral/systemic corticosteroid dose?

- ☐ Yes
- ☐ No

Is the patient currently being treated with biologic therapy?

- ☐ Yes, omalizumab

Start date: dd/mm/yyyy

Dose per injection visit\_\_\_\_\_ mg

Frequency of dosing\_\_\_\_\_ weeks

Has omalizumab dose or interval been changed in last 12 months:

- ☐ Yes, because of adverse effects
- ☐ Yes, because of insufficient response
- ☐ Yes, because of (very) good response
- ☐ No

- ☐ Yes, mepolizumab

Start date: dd/mm/yyyy

Dose per injection/visit\_\_\_\_\_ mg

Frequency of dosing\_\_\_\_\_ weeks

Has mepolizumab dose or interval been changed in last 12 months:

- ☐ Yes, because of adverse effects
- ☐ Yes, because of insufficient response
- ☐ Yes, because of (very) good response
- ☐ No

- ☐ Yes, reslizumab

Start date: dd/mm/yyyy

Dose per infusion/visit\_\_\_\_\_ mg

Frequency of dosing\_\_\_\_\_ weeks

Has reslizumab dose or interval been changed in last 12 months:

- ☐ Yes, because of adverse effects
- ☐ Yes, because of insufficient response
- ☐ Yes, because of (very) good response

☐ Yes, dupilumab

Start date: dd/mm/yyyy

Dose per injection/visit\_\_\_\_\_ mg

Frequency of dosing\_\_\_\_\_ weeks

Has dupilumab dose or interval been changed in last 12 months:

- ☐ Yes, because of adverse effects
- ☐ Yes, because of insufficient response
- ☐ Yes, because of (very) good response
- ☐ No

☐ Yes, benralizumab

Start date: dd/mm/yyyy

Dose per injection/visit\_\_\_\_\_ mg

Frequency of dosing\_\_\_\_\_ weeks

Has benralizumab dose or interval been changed in last 12 months:

- ☐ Yes, because of adverse effects
- ☐ Yes, because of insufficient response
- ☐ Yes, because of (very) good response

☐ No, patient is currently not treated with biologics

Does the patient currently use any of the following (non-pulmonary) medications?

- ☐ Nasal corticosteroids[L][SEP]
- ☐ Antihistamines[L][SEP]
- ☐ Bisphosphonates[L][SEP]
- ☐ Calcium suppletion ( $\pm$  vit D)[L][SEP]
- ☐ Proton pump inhibitors[L][SEP]
- ☐ vit K antagonists[L][SEP]
- ☐ NSAIDs[L][SEP]
- ☐ Other

-----  
-----  
-----

[L][SEP]

Has the patient received one of the following asthma add-on treatments  
IN THE PAST?

☐ omalizumab

If Yes, date of last administration (dd/mm/yyyy)

If yes, reason for stopping?

☐ insufficient reduction of systemic steroid dose[L]SEP

☐ Adverse effects[L]SEP

☐ Insufficient improvement of symptoms or exacerbations[L]SEP

☐ Insufficient improvement of lung function

☐ mepolizumab

If Yes, date of last administration (dd/mm/yyyy)

If yes, reason for stopping?

☐ insufficient reduction of systemic steroid dose[L]SEP

☐ Adverse effects[L]SEP

☐ Insufficient improvement of symptoms or exacerbations[L]SEP

☐ Insufficient improvement of lung function

[L]SEP

☐ reslizumab

If Yes, date of last administration (dd/mm/yyyy)

If yes, reason for stopping?

☐ insufficient reduction of systemic steroid dose[L]SEP

☐ Adverse effects[L]SEP

☐ Insufficient improvement of symptoms or exacerbations[L]SEP

☐ Insufficient improvement of lung function

[L]SEP

☐ benralizumab

If Yes, date of last administration (dd/mm/yyyy)

If yes, reason for stopping?

☐ insufficient reduction of systemic steroid dose[L]SEP

☐ Adverse effects[L]SEP

☐ Insufficient improvement of symptoms or exacerbations[L]SEP

☐ Insufficient improvement of lung function

[L]SEP

☐ dupilumab

If Yes, date of last administration (dd/mm/yyyy)

If yes, reason for stopping?

☐ insufficient reduction of systemic steroid dose[L]SEP

☐ Adverse effects[L]SEP

☐ Insufficient improvement of symptoms or exacerbations[L]SEP

- ☐ Insufficient improvement of lung function
- ☐ methotrexate[L][SEP]
- ☐ cyclosporine[L][SEP]
- ☐ azathioprine[L][SEP]
- ☐ cyclophosphamide
- ☐ interferon alpha
- ☐ aspirin desensitization
- ☐ macrolide therapy (>6 weeks)
- ☐ immunotherapy
- ☐ other: \_\_\_\_\_

Which steroid-induced adverse effects were ever objectively diagnosed?

- ☐ Skin bruising / thinning[L][SEP]
- ☐ Weight gain[L][SEP]
- ☐ Cataract
- ☐ Hypertension[L][SEP]
- ☐ Osteoporosis[L][SEP]
- ☐ Diabetes mellitus[L][SEP]
- ☐ Depression[L][SEP]
- ☐ Other: \_\_\_\_\_
- ☐ Other: \_\_\_\_\_
- ☐ Other: \_\_\_\_\_
- ☐ Other: \_\_\_\_\_

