## Participant Selection

### *Inclusion Criteria*

SHARP CENTRAL Registry concerns adult patients ( $\geq 18$  years) with severe asthma in the Europe. Severe asthma is defined according to international ERS/ATS guidelines (16). Briefly, this includes all adult asthma patients with uncontrolled symptoms for at least 6 months despite treatment with medium/high doses of inhaled corticosteroids, with or without oral corticosteroids, in combination with at least one other controller medication (e.g. long acting beta-2-agonists, theophylline), and having been checked for adherence to the medications, inhalation technique and co-morbid factors. These patients qualify for additional treatments for severe asthma, such as biologics. Some patients will already be using these therapies. Patients must be capable of giving informed consent and be able to travel to office/hospital for study visits.

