## Registry Duration

Patients will remain active in the registry until they voluntary withdraw or expire. Registry enrolment will be ongoing.

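### The CRF's current-inhaler lists are closed, with no 'other' line, no ICS/LABA/LAMA class and no 'none' answer, so some regimens have no designated entry and a blank is ambiguous

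*Protocol*

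**What the plan says.** The current-medication block of Appendix 1 (Case Report Form) opens with "Does the patients currently take one or more of the following medications" and continues "If yes, which one and at what dose". It then lists eight inhaler classes: SABA, anticholinergics, fixed SABA/anticholinergic combinations, single LABA, "ICS single inhaler", single LAMA, "Fixed ICS/LABA combination inhaler" and "Fixed LABA/LAMA combination inhaler". Each class has a tick box with named substances beneath it. Montelukast, theophylline and maintenance oral corticosteroids come next.

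Free text for current drugs appears only later, under "Does the patient currently use any of the following (non-pulmonary) medications". A further 'other' line belongs to the question on past add-on treatments. The biologics question, by contrast, ends with an explicit negative answer.

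Elsewhere in the protocol:
- The Primary Objective includes treatment strategies and responses to treatment.
- The Inclusion Criteria in Section 2 describe severe asthma by reference to "medium/high doses of inhaled corticosteroids" plus at least one other controller.
- Under Registry Duration, "Registry enrolment will be ongoing".
- Forms and data handling describes the appended CRF as complete.

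**The concern.** A fixed drug list is a weak instrument for a registry with no end date and sites across Europe, because it can record only the products foreseen when the form was written. Enrolment (under Registry Procedures) foresees adding questionnaires and diagnostic tests over time, but says nothing about updating the drug lists.

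At stake is the quality of core data. An analyst describing controller use or ICS dose must decide what an unticked class means. It could mean that the patient does not take the class, that the product was not on the list, or that the site did not complete the item. The form gives no means of choosing. If sites handle unlisted products differently, part of any difference between countries or calendar years could reflect coding practice rather than treatment.

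**Working it through.** No formula applies, and the protocol has no figure of its own to reproduce. The check is a reading of every option in the block and of every place where an unlisted inhaler might go.

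**1. Count the entries in each inhaler class.**

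| Class | Named substances or combinations | 'Other' line | 'None' answer |
|---|---|---|---|
| SABA | 2 | no | no |
| Anticholinergics | 1 | no | no |
| Fixed SABA/anticholinergic | 2 | no | no |
| LABA, single | 4 | no | no |
| ICS, single | 4 | no | no |
| LAMA, single | 3 | no | no |
| Fixed ICS/LABA | 5 | no | no |
| Fixed LABA/LAMA | 1 | no | no |
| Fixed ICS/LABA/LAMA | class absent | – | – |

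ICS-containing entries: 4 + 5 = 9. Triple-combination entries: 0. 'Other' lines across the eight classes: 0.

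**2. Look for another place to put an unlisted inhaler.** The 'other' entry for current drugs is limited to non-pulmonary medication, and the one for asthma add-on treatments is limited to the past. Neither can properly hold a current inhaler. The gap is not deferred to a fuller form, since the appended CRF is said to be complete.

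**3. Compare with the rest of the same form.** Appendix 1 provides 'other' for comorbidities, non-pulmonary drugs, past add-on treatments and steroid adverse effects, and an explicit negative for biologics. Both safeguards are in use elsewhere. The current-inhaler block has neither.

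**4. Test whether splitting into components always works.** A triple inhaler could be entered as a listed ICS/LABA plus a listed LAMA, but no instruction says so, and the record would then describe a two-device regimen. It also fails when a component is not listed. The lists are not complete by component even internally. Vilanterol appears only within one fixed combination and not among the single LABAs. The single-ICS list gives fluticasone without its ester, while the combination list names propionate in one entry and furoate in another.

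**5. Follow the data downstream.** Data Management and Quality Plan has the country databases exported, anonymised and merged, then mapped to a common data model. An analyst working from the merged file cannot go back to the source record to find out what a blank meant.

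**6. Consider size.** Let *u* be the share of patients whose ICS product has no entry, and suppose dose is unrelated to product. If every such blank is analysed as zero, the recorded mean dose is (1 − *u*) times the true mean. If the blanks are analysed as missing, the mean is not biased at all. The protocol gives neither *u* nor the handling rule, so any percentage would only restate an assumption.

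**The case against.** A reader might infer that every patient on an unlisted product is recorded as taking no inhaled steroid. The document does not support that, for four reasons:
- The form has no 'no ICS' answer, so a blank is ambiguous rather than a recorded negative.
- The ICS class boxes can be ticked without naming a product.
- A triple inhaler whose components are all listed can be entered in parts with their doses.
- An unlisted SABA, LABA, LAMA or LABA/LAMA product contains no steroid, so the inference cannot apply to it.

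The ICS adherence percentage on the same form also points to ICS use where adherence was checked.

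A reader might also infer that eligible patients would look ineligible. That does not follow either. Eligibility rests on the physician's diagnosis and the guideline definition at enrolment, the CRF is completed for patients already diagnosed, and nothing derives eligibility from the medication rows.

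There are partial safeguards too. Monitoring research progress provides for plausibility and completeness checks, comparison with source files and marking of missing data. Modification of the protocol allows changes. An ICS-free record would stand out, because the inclusion definition requires ICS.

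These arguments limit the consequence but do not remove the gap. A class box ticked alone, or an adherence percentage, gives no substance or dose. A monitor cannot mark an item as missing when an empty box is also the normal way to show that a drug is not taken. A query about a blank still has no designated field for its answer.

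**Conclusion.** The gap is real. The current-inhaler block consists of closed lists with no 'other, specify' line, no ICS/LABA/LAMA class and no explicit 'none'. Patients on an unlisted inhaler or a single-inhaler triple combination have no designated entry and sites have no entry rule, so substance and dose may be blank, split or inconsistently coded. For ICS-containing products, some patients may appear ICS-free or without a dose.

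This weakens the description of treatment strategies. It does not by itself show a bias of known direction or size. How many patients are affected depends on product use at the sites, which the protocol does not report, and on how blanks are handled in each project's analysis. The conclusion rests on the appended CRF being what sites use, as the protocol states. It is a data-capture weakness that should be corrected, and it does not invalidate the registry.

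**What to change.** Amend the current-inhaler block of Appendix 1 and the eCRF as follows:

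- Add to each inhaler class a line 'Other, specify substance(s) ___ and µg/day ___'.
- Add a fixed ICS/LABA/LAMA class with a separate dose for each component.
- Add 'none in this class' and 'unknown' answers to each class, so that a blank means missing.
- State one entry rule for combination inhalers, so that sites do not choose for themselves between splitting and free text.

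The cost is an eCRF edit and some free-text coding by data management. Records already entered would need a return to source files to resolve their blanks, so the change is cheaper the earlier it is made.

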### *Data Collection Schedule*

All data points collected for the registry will be collected as part of the asthma clinic. Investigators will be asked to evaluate participants at least once a year. The study calls for the documentation of annual assessments, with predefined range of tolerance of  $\pm 1$  month.

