## Early Withdrawal of Subjects

### *Investigator Withdrawal of Subjects*

Patients are followed every year in the severe asthma clinic as part of their standard of care. If a patient does not return to the clinic for any regularly scheduled visit, the patient will not be withdrawn but visits will be considered as missing data in the data set. The investigator will have the right to withdraw individual patients if they have evidence that the patient is wilfully giving incorrect information about their asthma. Such withdrawals would have to be discussed and authorised by the national lead and – in case of a strong dispute – mediated by the SHARP CRC.

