**[To be completed once every year by case-manager]**

Is patient lost to follow-up?

- ☐ yes
  - ☐ Patient passed away
  - ☐ Patient changed email address
  - ☐ Patient withdrew consent
  - ☐ Other \_\_\_\_\_
- ☐ No

Date of examination (dd-mm-yyyy):

Height: \_\_\_\_\_ cm  
 Weight: \_\_\_\_\_ Kg  
 BMI: \_\_\_\_\_ Kg/m^2

Smoking Status:

- ☐ Never Smoker[SEP]
  - ☐ Ex-Smoker (Quit smoking >12 months)
  - ☐ Current Smoker
- Current number of Pack years: \_\_\_\_\_

Has patient ever been admitted to ICU for asthma?

- ☐ Yes
- ☐ No

If yes, total number of ICU admissions:  
Has patient ever been intubated due to asthma?

- ☐ Yes
- ☐ No

If yes, total number of intubations:

Has the patient ever attended rehabilitation

- ☐ Yes
  - How often? \_\_\_\_\_ times
  - Last time \_\_\_\_\_ years ago
- ☐ No[SEP]
- ☐ Unknown

Has the patient ever undergone bronchial thermoplasty?

- ☐ Yes  
Date/year \_\_\_\_\_
- ☐ No[SEP]
- ☐ Unknown

Has spirometry ever been performed (If done multiple times, please report most current result)[SEP]

- ☐ Yes
- ☐ No

If Yes, when was most recent pulmonary function test performed? (dd/mm/yyyy)

If Yes, which values are available?

- ☐ Pre-bronchodilator values
- ☐ Post-bronchodilator values

|          | PRE
BRONCHODILATOR |                | POST
BRONCHODILATOR |                |
|----------|-----------------------|----------------|------------------------|----------------|
| FEV1     | L                     | %
predicted | L                      | %
predicted |
| FVC      | L                     | %
predicted | L                      | %
predicted |
| FEV1/FVC | %                     |                | %                      |                |

Has exhaled NO testing ever been performed?

- ☐ Yes
- ☐ No

If yes, please report date of most recent result:

FeNO \_\_\_\_\_ppb

Has CO diffusion capacity been performed (ever)?

- ☐ Yes
- ☐ No

If yes, please report date of most recent result:

DLCO: \_\_\_\_\_ mmol/min/kPa and \_\_\_\_\_ % predicted

Has bodyplethysmography (body box) ever been performed?

- ☐ Yes
- ☐ No

If yes, please report date of most recent result:

TLC: \_\_\_\_\_ L and \_\_\_\_\_ % predicted

RV: \_\_\_\_\_ L and \_\_\_\_\_ % predicted

Has bronchial provocation testing with methacholine ever been performed ?

- ☐ Yes
- ☐ No

If yes, please report date of most recent result:

- ☐ Positive (BHR demonstrated, FEV1 decline  $\geq 20\%$ )

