- ☐ Negative (BHR not demonstrated, FEV1 decline  $< 20\%$ )

Has blood cell differential counting been performed in the last 5 years?

- ☐ Yes
- ☐ No

If yes, please report date of most recent result:

- Leukocytes: \_\_\_\_ x 10E9 and \_\_\_\_ %
- Neutrophils: \_\_\_\_ x 10E9 and \_\_\_\_ %
- Eosinophils: \_\_\_\_ x 10E9 and \_\_\_\_ %

If yes, what was the highest eosinophil count ever measured?

Has blood glucose or HbA1c been measured during the last year?

- ☐ Yes
- ☐ No

If yes, please report date of most recent result:

Fasting glucose level:

Hba1c level

Has Blood Gas Analysis been performed/

- ☐ Yes
- ☐ No

If yes, please report date of most recent result:

pH \_\_\_\_\_ pCO2: \_\_\_\_\_ kPa / \_\_\_\_\_ mmHg; pO2: \_\_\_\_\_ kPa /  
\_\_\_\_\_ mmHg;

Has total serum IgE testing been performed?

- ☐ Yes
- ☐ No

If yes, please report date of most recent result:

\_\_\_\_\_ IU/ml or kU/l

Has a routine allergy test RAST/CAP or skin prick testing even been performed?

- ☐ Yes, positive
- ☐ Yes, negative
- ☐ No

If yes, please report date of most recent result:

Has allergy to aspergillus ever been tested?

- ☐ Yes, positive
- ☐ Yes, negative
- ☐ No

If yes, please report date of most recent result:

Has allergy to food ever been tested?

- ☐ Yes, positive
- ☐ Yes, negative
- ☐ No

If yes, please report date of most recent result:

Has sputum analysis (cell counts) ever been performed?

- ☐ Yes
- ☐ Yes, but inadequate sample
- ☐ No

If yes, please report date of most recent result:

\_\_\_\_\_ % Eosinophils  
\_\_\_\_\_ % Neutrophils

Has sputum culture been performed during last year?

- ☐ Yes, positive for pathogens
- ☐ Yes, negative for pathogens
- ☐ Yes, throat bacteria
- ☐ No

If yes, please report date of most recent result:

Has Chest X-Ray ever been performed?

- ☐ Yes, findings compatible with asthma[LSEP]
- ☐ Yes, findings compatible with other pulmonary disorders
- ☐ Yes, normal findings
- ☐ No

If yes, please report date of most recent result:

Has Chest HRCT ever been performed

- ☐ Yes

☐ No

If yes, please report date of most recent result:

- ☐ Bronchiectasis[L]  
[SEP]
- ☐ Emphysema
- ☐ Tree-in-bud configurations
- ☐ Other pulmonary abnormalities
- ☐ No abnormal findings

Has DEXA-scan ever been performed

- ☐ Yes, pathological findings
- ☐ Yes, normal findings
- ☐ No

If yes, please report date of most recent result:

Has bronchoscopy ever been performed

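### As printed, the CRF item on biologic dose or interval change has no 'No' answer for reslizumab and benralizumab, and the reason for a change made in the gap after a missed visit is lost

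*Protocol*

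**What the plan says.** The current-biologic part of the Protocol's Appendix 1 CRF lies in the section headed "To be completed once every year by case-manager". Each of the five biologics has a tick box for current treatment, a start date, dose and dosing frequency, and then a change item with a 12-month look-back: "Has reslizumab dose or interval been changed in last 12 months" and "Has benralizumab dose or interval been changed in last 12 months" are two of the five. All five list three reasons for a change: adverse effects ("Yes, because of adverse effects"), insufficient response and good response. None asks for the date of the change.

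On timing, Data Collection Schedule says "Investigators will be asked to evaluate participants at least once a year" and then "The study calls for the documentation of annual assessments, with predefined range of tolerance of" plus or minus one month. It does not say whether the window is counted from enrolment or from the previous visit. Under Investigator Withdrawal of Subjects, when a patient does not return for a scheduled visit, "the patient will not be withdrawn but visits will be considered as missing data in the data set".

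**The concern.** Treatment strategies and patient responses to treatment are part of the Protocol's primary objective. The reason a dose or interval was changed bears directly on both. In the CRF as shown, this item is also the only one that links a biologic still being taken to adverse effects.

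Two features weaken it. First, a patient on reslizumab or benralizumab whose dosing did not change has no box to tick, so a correct response and a skipped question look the same. Second, the look-back is fixed at 12 months, while the time between attended visits is not.

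Neither can be repaired in a later project-level analysis plan, because an answer, reason or date that was never collected cannot be reconstructed. Enrolment is open-ended, so the loss builds up each year.

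**Working it through.** The Protocol gives no rate, sample size or power figure for this item, so there is no stated figure to reproduce. The check compares the answer options and then applies interval arithmetic.

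**Step 1. Answer options (Appendix 1, current biologic therapy).**

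| Biologic | 'Yes' reasons | 'No' to the change item |
|---|---|---|
| omalizumab | 3 | present |
| mepolizumab | 3 | present |
| reslizumab | 3 | absent as printed |
| dupilumab | 3 | present |
| benralizumab | 3 | absent as printed |

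The 'No' printed after the benralizumab list answers the parent question (patient not on any biologic), so it cannot serve here.

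**Step 2. Effect of the missing 'No'.** Let N be the number treated (known from the tick box), c the true share with a change, and m the share of items not answered, taken as equal in changed and unchanged patients.

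- With a 'No' box: Yes/(Yes + No) = N·c·(1−m) / [N·(1−m)] = c.
- Without it, the only usable denominator is N: Yes/N = c·(1−m).

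Assumed ranges, as the Protocol gives none:

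| c | m = 0% | m = 10% | m = 20% | m = 40% |
|---|---|---|---|---|
| 5% | 5% | 4.5% | 4% | 3% |
| 10% | 10% | 9% | 8% | 6% |

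The relative understatement equals m, and m cannot be estimated from the form for these two drugs.

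**Step 3. Effect of the fixed look-back.** For an interval of L months between attended visits, uncovered time = max(0, L − 12) and overlap = max(0, 12 − L). Means assume visits spread evenly over the ±1 month window.

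| Situation | L (months) | Largest uncovered time | Mean uncovered time |
|---|---|---|---|
| Consecutive visits, window from previous visit | 11-13 | 1 (1/13 = 7.7%) | 0.25 (0.25/12 = 2.1%) |
| Consecutive visits, window from enrolment | 10-14 | 2 (2/14 = 14.3%) | 0.33 (0.33/12 = 2.8%) |
| One missed visit | 24 ± 2 = 22-26 | 14 (14/26 = 54%) | about 12 |

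For consecutive visits, mean overlap equals mean uncovered time by symmetry. After one missed visit the smallest uncovered time is 22 − 12 = 10 months (10/22 = 45%).

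**Step 4. What other fields recover.** Dose and dosing frequency are recorded each year, so a lasting change made in uncovered time appears as a difference between two attended visits. The reason and date do not appear, nor does a change that was later reversed.

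**The case against.** A fixed 12-month question asked once a year gives a 12-month period prevalence with the same exposure for every patient and visit. That is a legitimate measure and suits the cross-sectional analyses the Protocol foresees. For that measure, overlap between visits is not double counting and a gap is not bias. Simply replacing the 12-month wording would give unequal exposure and lose the prevalence. This stands, and any remedy must keep the prevalence derivable.

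Several stronger readings are tempting, but the documents do not support them:

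- A reader might infer that the visit window by itself loses or double counts a substantial share of changes. The 14% figure needs an enrolment anchor, which is not stated, and visits at opposite ends of the window. On average the effect is 2-3% of a year in each direction.
- A reader might infer that the two drugs have no denominator, or that 100% of patients would appear changed. The number treated is known from the tick box; the 100% arises only if 'Yes' answers are divided by 'Yes' answers. What is missing is the number who answered.
- A reader might extend the point to "Has blood glucose or HbA1c been measured during the last year" and to sputum culture. Both ask the date of the most recent result, and they record a result rather than count events.
- A reader might infer that adverse effects of biologics go unrecorded generally. Stopping a biologic has its own item, with the reason and the date of last administration. Adverse Event Reporting also says that systematic documentation of adverse events is not the primary purpose.

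Missing visits affect every yearly item, which is true. Here, though, the gap could be closed at the next attended visit, and the present wording prevents that. Plausibility checks and source verification may reduce non-response, but they do not supply the absent option. Finally, a 'No' line lost in reading the PDF cannot be excluded, although the text around both lists runs on without an obvious break.

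**Conclusion.** The point holds for dose and interval changes in patients still on a biologic, in two parts.

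The firmer part is the missing 'No' for reslizumab and benralizumab. The share of treated patients with a change is understated by the unknown non-response and is not comparable with the other three drugs. The size depends on assumed non-response: with 0-40% unanswered, a true 10% reads as 10% down to 6%. If non-response differs between changed and unchanged patients, the figure that matters is the non-response among those who changed. All of this rests on the form being as printed.

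The second part is the undated 12-month look-back. After one missed visit about 10 to 14 months are never asked about, and the reason for a change in that time is lost even when the dose and frequency fields show that one occurred. The loss is concentrated in patients who attend irregularly, so it need not be random. How often visits are missed is not stated, so no overall percentage is claimed. The ±1 month window is a minor contributor.

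**What to change.** (a) Check the source CRF for a line lost in PDF reading. If it is truly absent, add 'No' to the reslizumab and benralizumab change items, matching the other three.

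(b) Add the date of each change to all five items. At follow-up, ask for changes since the last completed registry visit; at baseline, keep the 12-month look-back. The dates allow 12-month prevalence to be derived as now, and rates can use the time actually covered. The statement under Study design that follow-up data are identical to baseline data would need a short qualification.

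Leave the glucose/HbA1c and sputum culture items as they are.

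The cost is two boxes, one date field per change, and a longer search of the patient file after a missed visit. The sponsor should also decide whether this counts as a change of procedures under Modification of the protocol. The change concerns data capture only and implies nothing about dosing.

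### The CRF's past-biologic page has no start date and only failure or harm as stopping reasons, so some treatment durations and all other reasons for stopping cannot be recorded

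*Protocol*

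**What the plan says.** Appendix 1 (Case Report Form) covers biologics twice, in the part that the case-manager completes each year.

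- **Current therapy.** Five drugs are listed: omalizumab, mepolizumab, reslizumab, dupilumab and benralizumab. Each has a start date, dose, dosing frequency and a question on dose or interval changes. The only other answer is "No, patient is currently not treated with biologics".
- **Past therapy.** The item opens "Has the patient received one of the following asthma add-on treatments" and concerns earlier use. For each of the same five drugs it asks "If Yes, date of last administration (dd/mm/yyyy" and a reason for stopping. The four boxes are "insufficient reduction of systemic steroid dose", adverse effects, "Insufficient improvement of symptoms or exacerbations" and too little gain in lung function. The past list ends with a free-text line for other treatments, which has no date or reason attached.

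Forms and data handling describes the attached CRF as complete. Study design says that the same data are collected at every annual visit, and Data Collection Schedule allows one month either side. Study objectives in the overview cover retrospective as well as prospective data on treatment and response. The text under Secondary Objectives adds the search for predictors of response and of adverse events. Registry Duration states "Registry enrolment will be ongoing".

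**The concern.** How long a patient stayed on a biologic, and why it was stopped, are basic data for any project on treatment patterns or response. The past page cannot supply the first for some courses, and it allows only unfavourable answers to the second. A stop because of good response, patient choice, pregnancy, loss of reimbursement or relocation has no box.

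The form is also inconsistent with itself. Dose changes may be attributed to a good response, but stops may not. Comorbidity items offer an unknown box, but stopping reasons do not. Past treatments and non-pulmonary medications have an other line, but current biologics do not.

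Projects on drug survival, switching or reasons for discontinuation would inherit these gaps. Unlike an analysis choice, they cannot be repaired in a later project's statistical analysis plan.

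**Working it through.** The protocol gives no figure to reproduce here. The check is a count of fields, followed by two short calculations whose inputs are assumptions and are marked as such.

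**Field count (Appendix 1)**
- Start date: 5 of 5 current biologics, 0 of 5 past biologics.
- Stopping reasons: 4 boxes in each of the five past blocks. Three are insufficient effect and one is adverse effects. None is neutral or favourable, and there is no other or unknown box.
- Entry for another biologic: 0 on the current item, 1 free-text line on the past list.

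**Which courses lack a start date**
- Ended before the baseline visit: never collected.
- Started and stopped between two annual visits: never collected. The nominal gap is 12 months. It reaches 12 + 1 + 1 = 14 months if one visit is a month early and the next a month late. One missed visit, which the protocol treats as missing data, makes the nominal gap 24 months.
- Current at one or more registry visits and stopped later: collected on the earlier form. The last-administration date follows on a later form, so duration can be derived by linkage.

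**Which in-registry courses are lost.** Assume visits exactly 12 months apart, all attended, and a start uniformly timed between visits. A course of d months (d < 12) is current at a visit with probability d/12, so it has no start date with probability 1 − d/12.
- d = 4: 1 − 4/12 = 67%.
- d = 6: 1 − 6/12 = 50%.
- d ≥ 12: 0%.

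Under these assumptions the loss falls on short courses, so durations taken from linked forms alone lean long.

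**Stopping reasons.** Let o be the share of stops that have some other reason. The true failure-or-harm share is 1 − o, and the share among recorded reasons is 1. The ratio is 1/(1 − o).
- o = 0.10: 1/0.90 = 1.11.
- o = 0.40: 1/0.60 = 1.67.

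The ratio is the same whether those stops are miscoded or left blank, because only the four boxes can be recorded. The two cases differ in the counts. Miscoding adds false failure codes. Blanks add none, but they cannot be told from ordinary missing data, so using all stops as the denominator is not a safe correction. The protocol gives no value for o.

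**The case against.** Several stronger readings are tempting, and the protocol does not support them.

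- **Biologic exposure is wrong throughout.** It is not. All five current drugs have a start date and the page is repeated yearly, so duration and switching can be derived for any course current at a registry visit. The Primary Objective in the detailed description speaks only of prospective data, which narrows the gap's reach. The overview's objectives do include retrospective data, however, and Inclusion Criteria expects some patients to be on these therapies at entry.
- **Every stop is forced into a failure or harm code.** Nothing makes the item mandatory. Data Quality describes coded answers where possible, and Monitoring research progress says that missing data are marked. A stop for another reason may simply be blank. That removes the false code but not the one-sided record.
- **Treated patients already sit in the untreated group.** The protocol names no asthma biologic beyond the five listed. A separate item flags patients receiving study medication for asthma in a trial, though it does not ask which drug. The missing box is a coverage risk, not a demonstrated misclassification.
- **Dose-change rates cannot be compared between drugs.** In the text as read, "Has reslizumab dose or interval been changed in last 12 months" and "Has benralizumab dose or interval been changed in last 12 months" have no No box, unlike the other three drugs. This may be a fault of text extraction, so nothing here rests on it.

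It is also fair to say that the protocol sets no drug-survival or discontinuation endpoint, that each project brings its own analysis plan, and that response is measured by annual questionnaires, lung function and steroid dose as well. These points lower the priority. They do not fill the missing fields.

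**Conclusion.** The point holds in a limited form and should be fixed, though it does not undermine the registry as a whole.

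- **Duration** cannot be derived for courses that ended before entry or that fell wholly between two annual visits. For other courses it can, provided a participant's annual forms stay linked in the merged file, as the planned longitudinal analyses already require.
- **Stopping reasons** are one-sided by design: failure or harm is 100% of what can be recorded. The 1.11 to 1.67 overstatement rests wholly on an assumed 10% to 40% of stops for other reasons and shows scale only.
- **Another current biologic** cannot be entered. Such a patient would be coded as untreated or left blank. With open-ended enrolment, and with Adverse Event Reporting expecting many participants on novel biologics, this is foreseeable but not shown to have happened.

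**What to change.** - Add a start date for each past biologic.
- Extend the stopping reasons with good response, patient choice, pregnancy, reimbursement or access, other (specify) and unknown.
- Add an entry for another current biologic, with its name, start date, dose and interval.
- Check the laid-out form for a No box on the reslizumab and benralizumab dose-change items, and add it if it is truly absent.

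The cost is a few eCRF fields and one query round for records already entered. A formal amendment with ethics approval under country rules may also be needed (Modification of the protocol). Acting early helps: no further data may be collected once a participant withdraws, so their gaps become permanent.
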